At the treatment site in Johannesburg where the study team is based, the average interval between the first CD4 count that indicates treatment eligibility and treatment initiation is 42 days among those who do start treatment within 16 weeks and entails an average of 4 visits to the site. Even very sick patients usually face a delay of at least 2 weeks before initiation. In addition to delay in starting treatment, each clinic visit entails time, transport costs, and possibly child care and other costs for the patient. Previous research at the same site estimated that the median cost to an ART patient per clinic visit was R29 (\$4.15) (inflated to 2011 prices) for transportation alone, the equivalent of roughly a third of a day's wage for a domestic worker. Each visit also required a median of two hours' travel time. A more recent study found that, due largely to waiting time, the average duration of a routine clinic visit for a stable ART patient at this site is just under 6 hours; even simply picking up medication, without any clinical consultation, requires nearly 3 hours. Requiring multiple visits before dispensing medications thus constitutes a major obstacle to treatment initiation, in addition to other possible reasons for loss to follow up.

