##### 4b. Secondary objectives

1. For non-pregnant adults, compare the cost per patient alive, in care, and virally suppressed within 10 months of an HIV test or enrollment in HIV care for those offered rapid ART initiation to the cost for those offered standard care.
2. For pregnant women, estimate the cost per patient adhering to ART through delivery and the cost per infant infection avoided, using estimated vertical transmission rates.
3. Estimate the proportion of patients alive, on ART, and virally suppressed at 6 month intervals after treatment initiation and at the final date of data censoring.
4. Estimate the average time interval between HIV test or first HIV or ANC care visit and treatment or PMTCT initiation before and after rapid ART initiation became the guideline procedure for pregnant women.
5. If enrollment numbers allow, among pregnant women, stratify the primary outcome (the proportions of subjects achieving retention on ART or PMTCT regimen until delivery) by CD4 count > 350 and  $\leq 350$ .
6. Compare the average gestational age at ART initiation and average number of weeks on ART prior to delivery for pregnant women before and after rapid ART initiation became available.
7. Identify patient-level predictors of treatment uptake, retention in care, and viral suppression.
8. Describe the prevalence of TB symptoms and confirmed TB, time to initiation of TB treatment, and time to initiation of ART among patients with TB.
9. Evaluate the feasibility of the rapid initiation strategy in terms of patient acceptance, actual time between HIV test/enrollment in care and dispensing of first dose of ARVs, and patient costs incurred.

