#### 8e. Medical record data

Most data for the study will be collected from the site's routinely maintained electronic medical records, which are maintained in an information system called Therapy Edge-HIV™. Records in this information system are typically only created once a patient starts ART. Paper-based medical records kept by the site will therefore be used to supplement the electronic medical record system as needed. The fields to be collected are listed below.

*To be used to link electronic and paper-based records to study identification number only:*

- Electronic medical record system number
- Clinic file numbers
- National ID number
- Name
- Date of birth

*All subjects at baseline (ART initiation):*

- Date of positive HIV test (if available)
- Sex
- Age in years
- Weight and height or BMI
- Date treatment eligibility determined, if reported
- Date and result of eligibility-determining CD4 count
- Date and result of TB symptom screen
- Date, type, and result of TB test(s)
- TB treatment, if relevant
- WHO stage and clinical conditions
- Date ART initiated (first dose of drugs dispensed)
- First-line regimen prescribed

*For all clinic visits for duration of study follow up, including initial visit and pre-ART visits (to be used to estimate resource utilization):*

- Date of visit
- Primary reason for visit (e.g. scheduled medical visit, medication pickup, unscheduled medical visit)
- Types of professionals seen (e.g. nurse, doctor, pharmacy assistant, counselor)
- Group and individual sessions attended (e.g. wellness course, adherence education)
- Numbers and types of all lab tests conducted (including CD4 counts and viral loads)
- Other procedures (e.g. x-rays) performed

- Medications prescribed and dispensed (ARV and non-ARV)
- Admissions for inpatient care since previous visit, if recorded
- Details of inpatient care received (facility, number of days, medications, lab tests, etc.) if recorded

*At interim and final dates of data censoring:*

- Date and result of most recent viral load test
- Status at clinic (in care / died / transferred to another site / stopped care / lost to follow up, defined as > 1 month late for last medication pickup)
- New or recurring HIV-related conditions
- Date and cause of death if applicable
- Date and result of most recent CD4 count

*Track 2 subjects only (pregnant women):*

- Gestational age at diagnosis or first ANC visit for current pregnancy if previously diagnosed
- Prior exposure to PMTCT

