#### *11a ii. Secondary outcomes*

Secondary outcomes will include:

1. Average cost per patient who is alive, in care, and virally suppressed within 10 months of study enrollment (Track 1).
2. Cost per patient adhering to ART through delivery and the cost per infant infection avoided, using estimated vertical transmission rates (Track 2).
3. Proportion of subjects in each track and group alive, on ART, and virally suppressed at six-month intervals and the final date of data censoring.
4. Average time to ART initiation (days) for each track and group.
5. For Track 2, average gestational age at ART initiation (weeks) and average duration (weeks) on ART prior to delivery.
6. For Track 2, if enrollment numbers allow, proportion of subjects with CD4 count > 350 and ≤ 350 achieving the primary outcome of retention on ART (or PMTCT regimen) until delivery.
7. Patient-level predictors of treatment uptake, retention in care, and viral suppression.
8. Prevalence of TB symptoms and confirmed TB, time to initiation of TB treatment, and time to initiation of ART among patients with TB.
9. Process indicators including:
  - Acceptance of rapid initiation strategy (% of patients offered rapid initiation who accept)
  - Average time elapsed (days) between HIV test and dispensing of first dose of ARVs
  - Average cost to patients of initiating treatment, including travel and other out-of-pocket costs and time spent in clinic

All outcomes will be estimated for each study population and compared between the two study populations where relevant.

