#### 11b. Clinical outcomes analysis

For both tracks and for primary and secondary clinical outcomes, the analytic approach for clinical outcomes will be the same. All analyses will be by intention-to-treat: subjects will be analyzed according to the intervention they were supposed to receive, whether or not they adhere to the defined intervention.

The analysis will begin with a simple comparison of the two treatment groups with respect to baseline predictors of outcomes. We will then conduct a crude analysis comparing the proportion of patients achieving each dichotomous outcome by group and crude risk ratios and 95% confidence intervals

stratified by group. For average gestational age at ART initiation and average time on ART before delivery for Track 2, we will calculate the mean difference between groups and corresponding 95% confidence interval.

Since adherence has been a particular concern for pregnant women who were not eligible for ART under the previous guidelines, the primary outcome for Track 2 will be stratified in secondary analysis by CD4 count at the time of initial ANC visit if enrollment numbers by the end of the study period are large enough to allow a stratified analysis. Subjects in the prospective group found after ART initiation to have CD4 counts above 350 will be compared to those in the retrospective group who were offered AZT under the previous guidelines, while subjects in the prospective group found after ART initiation to have CD4 counts below 350 will be compared to those in the retrospective group who were offered full ART under the previous guidelines.

Because we will not be randomizing large numbers of patients in Track 1 and because no randomization will occur in Track 2, it is possible that some baseline covariates may be imbalanced by treatment arm. To adjust for potential differences by baseline covariates, a log-linear regression model will be used to estimate adjusted risk ratios and a linear regression will be used to adjust mean differences.

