Variables considered to be important in the univariate stage will be included in multivariate models. Adjusted analyses will include covariates which are unevenly distributed across groups and which could plausibly affect viral suppression or time to ART initiation. These potential confounders include demographic (e.g. age, sex) and socioeconomic (education, distance from clinic, employment, etc.) variables, medications, baseline CD4 counts, prior receipt of PMTCT, and low BMI, among others. Each of these models can then be used to look for patient-level predictors of treatment uptake, viral suppression, and retention in care.

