#### 11d. Analysis of process indicators

In order to help inform treatment providers and policy makers of the implications of rapid ART initiation in terms of patient acceptance, impact on staff, laboratory work flow, and other patient-level and health systems factors, we will generate descriptive statistics for process indicators for both initiation strategies, including:

- Acceptance of rapid initiation strategy (% of patients offered rapid initiation who accept and frequency of reasons for refusals where provided)
- Mean time elapsed (days) between HIV test and dispensing of first dose of ARVs
- Mean time (hours: minutes) spent in clinic by patients receiving rapid and standard initiation, based on recorded start and end time for each clinic visit.
- Mean cost (rand) to patients of making the clinic visits required for treatment initiation, including transport fares, lost wages, and other costs reported in the baseline questionnaires.

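### In Track 1, time to ART is planned as a mean number of days, which only starters can contribute to, so the comparison is not intention-to-treat and may be too small or too large

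*Protocol*

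**What the plan says.** Section 11a ii (item 4) defines the outcome as "Average time to ART initiation (days) for each track and group". Section 11d lists among the process indicators "Mean time elapsed (days) between HIV test and dispensing of first dose of ARVs".

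Section 11b says that the analytic approach is the same for both tracks and for all clinical outcomes. On adjustment for baseline imbalance it says that "a linear regression will be used to adjust mean differences". It chooses adjustment covariates among those "which could plausibly affect viral suppression or time to ART initiation". It also states: "All analyses will be by intention-to-treat: subjects will be analyzed according to the intervention they were supposed to receive".

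Section 8e records the ART start date as the date on which the first drugs are dispensed, so a subject who never reaches dispensing has no date. The protocol does not assign such subjects a value, censor them, set a horizon or name a time-to-event method.

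The primary outcome is handled differently. Section 11a i counts every eligible patient without a six-month viral load within 10 months as a failure, so non-starters stay in the denominator.

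**The concern.** Whether a patient starts ART is itself what the intervention is meant to change. Section 12a i expects fewer treatment-eligible patients to be lost before starting. Section 3c expects some rapid-arm patients to start who would otherwise have started later or never. Section 6c v keeps rapid-arm subjects who return after 28 days in the rapid group for analysis, although they are then initiated under standard procedures. A mean of observed days therefore compares the starters of one arm with a differently selected set of starters in the other. Randomization does not protect that comparison.

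The result at stake is how much sooner patients get treatment under the rapid strategy. No other listed outcome clearly fills the gap. Item 7 of section 11a ii concerns predictors of uptake, and the acceptance indicator covers only those offered rapid initiation. No between-arm comparison of the proportion starting ART by a fixed day is listed.

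**Working it through.** **The plan's own figures.** The protocol gives no planned value or power for time to ART. Its prior-site data give a starters-only average: in section 3b, "treatment initiation is 42 days among those who do start treatment within 16 weeks". Section 10 says that 46% of eligible patients started within 16 weeks, and its product reproduces: 0.46 × 0.77 = 0.354, or 35%.

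**One arm, prior-site figures.** Let p be the share starting by horizon T, and m the mean days among those starters. The mean time without ART up to T over all eligible patients is

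R(T) = p·m + (1 − p)·T.

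With p = 0.46, m = 42 and T = 16 × 7 = 112 days:

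R(112) = 0.46 × 42 + 0.54 × 112 = 19.32 + 60.48 = 79.8 days, against 42 days among starters.

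R(T) exceeds m whenever p < 1 and m < T, so the starters' mean is too low as a measure of time without ART in either arm.

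**Two arms, illustration.** Start shares implied by the design, if 77% suppression applies in both arms, are 0.50/0.77 = 65% (standard) and 0.70/0.77 = 91% (rapid). Further assumptions are 42 days among standard starters, 7 days among rapid starters, and 300 days for 10 months, with the same shares and means used at both horizons. With 200 enrolled per arm, 0.35 × 200 = 70 standard and 0.09 × 200 = 18 rapid subjects would have no value.

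The starters-only difference is 42 − 7 = 35 days whatever the start shares. Over all subjects:

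- T = 112: standard 0.65 × 42 + 0.35 × 112 = 66.5; rapid 0.91 × 7 + 0.09 × 112 = 16.45; difference about 50 days.
- T = 300: standard 27.3 + 105 = 132.3; rapid 6.37 + 27 = 33.37; difference about 99 days.

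The rapid start share is then varied, with the standard share kept at 65%:

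| Rapid start share | Starters only | All subjects, T = 112 | All subjects, T = 300 |
|---|---|---|---|
| 65% | 35 | 22.8 | 22.8 |
| 70% | 35 | 28.0 | 37.4 |
| 80% | 35 | 38.5 | 66.7 |
| 91% | 35 | 50.1 | 98.9 |

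With equal shares, the all-subjects difference is p times the starters-only one (0.65 × 35 = 22.75), so the planned statistic overstates. It starts to understate where 66.5 − [7p + 112(1 − p)] = 35, that is p = 80.5/105 = 77% at T = 112. At T = 300 the threshold is p = 202.7/293 = 69%.

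At shares of 65% and 91%, an assumed rapid starters' mean of 1 to 28 days gives a starters-only difference of 41 to 14 days. Over all subjects it is 56 to 31 days (T = 112) or 104 to 80 days (T = 300).

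**The case against.** **Restriction to starters is inferred.** The protocol never says that the average is taken among starters, and a statistical analysis plan, not seen here, could deal with non-starters. That is fair. But the protocol itself chooses the statistic and the adjustment method, and a mean of observed days has nothing to average for a non-starter. The general intention-to-treat sentence does not supply a value.

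**Much of it is descriptive.** Section 11d calls the process indicators descriptive, and section 11b assigns unadjusted mean differences only to two Track 2 variables. A Track 1 linear regression on days is therefore not written out. It remains the natural reading, because the approach is common to both tracks and time to ART guides the choice of covariates. This limits the weight of the point without removing it.

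**Stronger readings that a reader might infer, which the documents do not support:**

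- *That the plan would report 42 days and be wrong by 38.* The 42 days is a prior-site average truncated at 16 weeks and counted from the first eligible CD4 count. Section 3a ties the 46% to a CD4 limit of 250 and to time from HIV testing, whereas the trial uses 350. The trial has no 16-week cut, so later starters would raise its mean.
- *That the benefit is always understated, or could be reversed.* The direction depends on the start shares, as shown. Against a standard mean of 42 days, reversal would need a rapid starters' mean above 42, and nothing in the protocol suggests one.
- *That outcomes at six-month intervals share the defect.* Section 4b does say "virally suppressed at 6 month intervals after treatment initiation and at the final date of data censoring", but item 3 of section 11a ii defines a proportion of subjects in each track and group. At most the time origin needs aligning.
- *That Track 2 loses randomization, or that its never-starters should score zero weeks on ART.* Track 2 is not randomized. Section 11b says that some women in its retrospective group were offered AZT, so a zero score could penalise that group by design.
- *That non-starters drop out of the trial.* They count as failures in the primary outcome.

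**Conclusion.** The point holds for Track 1, for secondary outcome 4 and the matching process indicator. As fixed, the measure leaves out non-starters, whose number the intervention is expected to change. The resulting difference is not an intention-to-treat effect and cannot be read as the time gained by the strategy.

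That each arm's average time without ART is understated follows from the arithmetic whenever some subjects do not start. The size cannot be known in advance. The 79.8 against 42 days is a one-arm illustration from another population. The between-arm results rest on the assumed start shares, starters' means and 300-day horizon, and they go either way. The matter is secondary, should be corrected, and leaves the primary outcome and its sample size untouched.

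**What to change.** For Track 1, define the outcome as time from randomization or study enrollment (one origin, the same in both arms) to first dispensing, in all enrolled eligible subjects.

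- Report by arm the cumulative incidence of ART start at prespecified days up to 10 months, and the difference in restricted mean time to ART over that horizon, with confidence intervals.
- Censor non-starters at 10 months.
- Treat recorded deaths as competing events. State that deaths among those lost are incompletely known, since section 12g says they surface only if household members report them to the clinic.
- State how transfers are handled, for example using the new clinic's records where the consent addendum of section 6e ii was signed, with a sensitivity analysis for the rest.
- Keep the mean among starters, labelled as descriptive and shown with the number of subjects it omits.

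The cost is a change of wording and slightly more analysis work. Sections 8c and 8e already collect enrollment, dispensing and recorded death dates, and section 8f ii provides for monthly review of standard-group files. No new data are needed.

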- Nearly half of those who are eligible for ART (49%) do not return to obtain their CD4 count results within 3 months, and are thus not aware of their need for treatment; and
- Even among those who do receive their CD4 count results and are eligible or fast-tracked for ART (CD4  $\leq$  250) fewer than half (46%) initiate ART within four months of HIV testing.

This problem is likely to be even worse among patients who obtain an HIV test from a mobile or stand-alone HIV counseling and testing site, and thus must be referred elsewhere for a CD4 count and other services. South Africa's recent raising of the treatment eligibility threshold to CD4  $\leq$  350 is likely to exacerbate this problem further, as more asymptomatic patients become eligible.

Failure to initiate ART promptly is also an acute problem amongst pregnant women who are diagnosed with HIV during antenatal care. A study in Cape Town, South Africa found that only half (51%) of pregnant women who were eligible for full HAART (three drug treatment regimen rather than PMTCT regimen) under previous guidelines (CD4 count  $< 200$  cells/mm^3) initiated treatment prior to delivery, increasing the risk both to themselves and to their infants.

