#### *Exclusion criteria:*

- Currently on ART or on ART at any time in the past 12 months (three-drug combination; previous PMTCT regimen exposure for an earlier pregnancy is not an exclusion criterion)
- Stated intention to seek further HIV care during the next 12 months or antenatal care before completion of the current pregnancy at another site, not at the study site
- Not physically or emotionally able to participate in the study, in the opinion of the investigators
- Not willing or able to provide written informed consent to participate in the study

- Previously enrolled in the same study
- Diagnosed with drug-resistant TB or on MDR-TB treatment
- For Track 1 only, pregnant (pregnancy is an exclusion criterion for Track 1 because treatment guidelines for pregnant women differ from those for non-pregnant adults)

*\*Current South African treatment eligibility criteria for non pregnant HIV-positive adults are:*

- *CD4 count  $\leq$  350; or*
- *Tuberculosis, regardless of CD4 count; or*
- *WHO Stage 4 or Stage 3 condition, regardless of CD count (hereafter “Stage 4/3”)*

*All pregnant HIV-positive women are eligible for ART.*

Subjects in Track 1 will be followed prospectively and will be asked for written informed consent prior to study enrollment. An additional Track 1 retrospective comparison group will be enrolled comprised of patients who became eligible for ART at one of the two study sites (Thuthukani Clinic) prior to the launch of the study, with data collection limited to retrospective medical record review. In Track 2, subjects offered rapid initiation by the study clinic under the new standard of care will be followed prospectively and asked for written informed consent before study enrollment. For subjects in the comparison group in Track 2, data will be collected retrospectively through medical record review only. The study team will have no contact with these subjects, and informed consent will not be sought.

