Track 2: The primary outcome for Track 2 is the proportion of subjects in each group who adhere to ART or the prior PMTCT regimen until delivery. The number of weeks a pregnant woman is on ART before delivery is the most important predictor of perinatal HIV transmission. The guideline change to immediate ART initiation for pregnant women is likely to lead to earlier initiation for most pregnant women, but the intervention will be effective only if patients adhere to ART through the duration of pregnancy. Adherence will be measured as making monthly medication pickups to allow a continuous supply of ARVs through delivery. The analysis period for the primary outcome will start on the day of study enrollment, which is the date of a positive HIV test or the first antenatal visit of the current pregnancy, for women previously diagnosed, and end at the actual or estimated delivery date.

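### Two Track 2 secondary outcomes count ART only, so pre-group women given AZT or nothing have no gestational age at initiation and no stated value for weeks on ART

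*Protocol*

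**What the plan says.** Item 5 of section 11a ii defines two outcomes: "For Track 2, average gestational age at ART initiation (weeks) and average duration (weeks) on ART prior to delivery". Secondary objective 6 in section 4b sets the same comparison, also for ART only. Section 11b fixes the estimator: "For average gestational age at ART initiation and average time on ART before delivery for Track 2, we will calculate the mean difference between groups", with a 95% confidence interval and linear regression for adjustment.

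Three other statements bear on it.

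- **Who is in the pre group.** Section 11b compares post-group women with CD4 above 350 with "those in the retrospective group who were offered AZT under the previous guidelines". It sets these women apart from pre-group women who were offered full ART.
- **What ART means.** The exclusion criteria gloss it: "Currently on ART or on ART at any time in the past 12 months (three-drug combination". They treat earlier PMTCT exposure as something else. Section 3a draws the same line.
- **Who is analysed.** Section 11b: "All analyses will be by intention-to-treat: subjects will be analyzed according to the intervention they were supposed to receive", whether or not they adhere to it.

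The regimen counted changes from place to place:

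| Place | Regimen counted |
|---|---|
| 4b objective 4 (time to start) | "treatment or PMTCT initiation before and after rapid ART initiation became the guideline procedure for pregnant women" |
| 11a ii item 4 (time to start) | ART only |
| 4b objective 6 and 11a ii item 5 | ART only |
| 11a i, Track 2 primary outcome | "proportion of subjects in each group who adhere to ART or the prior PMTCT regimen until delivery" |
| 4b objective 5 and 11a ii item 6 | ART or PMTCT regimen |

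**The concern.** A mean gestational age at ART initiation can be taken only over women who started ART. In the post group that should be nearly everyone, because the guideline offers ART to all pregnant women at the first antenatal visit. In the pre group it is the women whose CD4 count qualified them for ART and who also started before delivery. The two means then describe differently selected women. Selection depends on starting treatment, which is what the guideline change was meant to alter.

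Weeks on ART before delivery is a different case. Zero is a meaningful value for a woman who never received ART, but the protocol does not say whether she counts as 0 or as missing. Section 11a i calls time on ART before delivery the most important predictor of perinatal transmission, so the choice matters for how Track 2 will be read.

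**Working it through.** The protocol gives no planned value for either outcome and no share of pre-group women on AZT or never started, so there is no figure to reproduce. The check asks how large the unscored share could be, and what leaving it out does to each outcome.

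**1. Share of the pre group without an ART start**

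Share = 1 − (share eligible for ART × share of eligible women who start before delivery).

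Inputs, all proxies from other populations:
- eligible: 54% (section 3a, outpatient HIV testers) or 70% (section 10, Track 1 planning for non-pregnant adults);
- starting: 51% (section 3a, Cape Town, CD4 below 200: "only half (51%) of pregnant women who were eligible for full HAART" started before delivery). The other start rates below are assumed values, up to 100%.

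| Start rate among eligible | 54% eligible | 70% eligible |
|---|---|---|
| 51% | 1 − 0.275 = 72% | 1 − 0.357 = 64% |
| 77% | 1 − 0.416 = 58% | 1 − 0.539 = 46% |
| 88% | 1 − 0.475 = 52% | 1 − 0.616 = 38% |
| 100% | 46% | 30% |

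Section 10 allows up to 152 record-review women in Track 2. Of these, about 42 (152 × 0.275) to 106 (152 × 0.70) would have an ART start date.

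**2. Weeks on ART before delivery**

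Let s and t be the shares starting ART in the pre and post groups, and m_pre and m_post the mean weeks among starters.

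- Starters only: m_post − m_pre.
- All women, non-starters scored 0: t × m_post − s × m_pre.

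Illustrative means (assumed): m_post = 16, m_pre = 10. Starters only gives 16 − 10 = 6.0 weeks. With zeros counted:

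| s | t = 1 | t = 0.88 |
|---|---|---|
| 0.28 | 16 − 2.8 = 13.2 | 14.08 − 2.8 = 11.3 |
| 0.36 | 16 − 3.6 = 12.4 | 14.08 − 3.6 = 10.5 |
| 0.70 | 16 − 7.0 = 9.0 | 14.08 − 7.0 = 7.1 |

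The t = 0.88 column is a cautious case. The 88% in section 3c is same-day initiation in a Cape Town pilot, so 12% is at most the share never starting there. Dropping non-starters understates the difference whenever (1 − s) × m_pre exceeds (1 − t) × m_post. In these examples the left side is at least 0.30 × 10 = 3.0 and the right side at most 0.12 × 16 = 1.9.

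**3. Gestational age at initiation**

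Illustrative values (assumed): post mean 22 weeks, pre-group ART starters' mean 24 weeks, s = 0.36. Starters only gives 24 − 22 = 2.0 weeks. Now give the other 64% a regimen start at g weeks:

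- g = 28: 0.36 × 24 + 0.64 × 28 − 22 = 4.6 weeks
- g = 24: 2.0 weeks
- g = 20: 0.36 × 24 + 0.64 × 20 − 22 = −0.6 weeks

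The difference can grow, stay the same or change sign. A woman who starts nothing has no g at all, so no mean can include her.

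**The case against.** The strongest reply is that ART is loose shorthand in Track 2. Objective 2 in section 4a and the overview in 5a speak of adherence to ART, yet the same outcome in 11a i covers ART or the prior PMTCT regimen. On that reading, women on AZT do have a start date and a duration, and only women who started nothing remain a problem. This is plausible and would shrink the affected share. But the protocol also uses ART in the strict sense, and item 5 sits directly above an item that names the PMTCT regimen, so the text does not settle it.

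A second reply is that scoring rules for secondary outcomes belong in the SAP. That is fair for weeks on ART: section 8e collects weeks on ART at delivery, and 0 is a natural entry. It is weaker for gestational age, because 11b itself fixes an estimator that cannot include non-starters.

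Three stronger readings are tempting, and the documents do not support them.
- A reader might infer that the plan drops these women from both outcomes. No section says so, and weeks on ART can be scored.
- A reader might infer that most of the pre group is lost. That rests on the 51% from another city under a CD4 threshold of 200. At 70% eligible it fails once more than 0.5 / 0.7 = 71% of eligible women start. Selection from the site's PMTCT register could also change the mix.
- A reader might infer that both outcomes understate the guideline's effect. That follows only for weeks on ART, and only if non-starters are dropped.

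The stakes are also limited: these are secondary outcomes in an observational track, and the Track 2 primary outcome covers both regimens.

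**Conclusion.** The point holds in a limited form. Mean gestational age at ART initiation, as defined, can be taken only over starters. It therefore compares nearly the whole post group with a selected part of the pre group, at odds with the intention-to-treat statement in the same section, and the direction of the bias is unknown. Weeks on ART has a workable value for every woman, but the protocol does not state it. If non-starters are dropped, the difference is understated: in the illustration, 6.0 weeks against 9.0 to 13.2 when every post-group woman starts.

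Roughly 30% to 72% of the pre group may be affected under the strict ART reading. That range comes from proxies for other populations and is not a bound; higher eligibility would lower it. The conflict in regimen wording between sections does not depend on any of these assumptions.

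**What to change.** - **Regimen.** In 4b objectives 4 and 6, 11a ii items 4 and 5, and 11b, name the same regimens: ART or the prior PMTCT regimen, with three-drug ART reported separately.
- **Weeks before delivery.** Analyse all women, with those who did not start the regimen in question scored 0. Use a bootstrap or robust interval, because the values will be skewed with a spike at zero.
- **Timing.** Compare the cumulative proportion of all women started by gestational week up to delivery, keeping never-starters in the denominator. Report mean gestational age at initiation only as a description among starters, beside the proportion who started. Amend objective 6 to match.

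The cost is minor wording and a little analysis code. Section 8e already collects the ART start date, drugs dispensed, pickup dates, delivery date and weeks on ART at delivery. It lists no separate AZT start date, so that would be derived from the dispensing and pickup records.
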